## Abstract

Infant allergy is the most common early manifestation of an increasing propensity for inflammation and immune dysregulation in modern environments. Refined low-fibre diets are a major risk for inflammatory diseases through adverse effects on the composition and function of gut microbiota. This has focused attention on the potential of prebiotic dietary fibres to favourably change gut microbiota, for local and systemic anti-inflammatory effects. In pregnancy, the immunomodulatory effects of prebiotics may also have benefits for the developing fetal immune system, and provide a potential dietary strategy to reduce the risk of allergic disease. Here, we present the study protocol for a double-blinded, randomised controlled trial investigating the effects of maternal prebiotics supplementation on child allergic disease outcomes. Eligible pregnant women have infants with a first-degree relative with a history of medically diagnosed allergic disease. Consented women are randomised to consume either prebiotics (galacto-oligosaccharides and fructo-oligosaccharides) or placebo (maltodextrin) powder daily from 18–20 weeks’ gestation to six months’ post-partum. The target sample size is 652 women. The primary outcome is infant medically diagnosed eczema; secondary outcomes include allergen sensitisation, food allergies and recurrent wheeze. Breast milk, stool and blood samples are collected at multiple timepoints for further analysis.

## 1. Introduction

Allergic diseases are now among the most common chronic diseases of childhood, with eczema/atopic dermatitis now affecting up to one-in-five infants and food allergy in one in ten infants in affluent societies [1]. Eczema/atopic dermatitis and food allergies commencing during infancy are the earliest manifestations of allergy, and reflect the vulnerability of the immune system to modern diet, lifestyle and environmental changes. Diet is a major determinant of gut microbiota composition and function [2,3], which in turn can be associated with inflammation and immune dysfunction [4]. Hence, the role of dietary composition in increasing commensal microbial gut diversity has emerged as one of the critical factors for beneficial immune health. 

Prebiotics are defined as substrates that are selectively utilized by host microorganisms conferring a health benefit [5]. Prebiotics are recognized as key immune-modulating nutrients, which selectively stimulate growth of beneficial gut microbiota—with prebiotic fermentation products, such as short-chain fatty acids (SCFA), that have direct local gut and systemic anti-inflammatory effects [5]. Microbial-derived SCFA are recognised as essential mediators in the communication between the intestinal microbiome mucus barrier and the immune system, and are considered as a likely pathway by which the gut microbiota influences immune health [6]. SCFA influence host immune responses through several key pathways [7] including: (1) promoting intestinal barrier integrity; (2) binding to ‘metabolite-sensing’ G-protein-coupled receptors such as GPR43, GPR41, and GPR109A, which promote gut homeostasis and the regulation of inflammatory responses [8,9,10]; and (3) inhibition of Histone Deacetylases which regulate rapamycin (mTOR)-S6K pathways required for T cell differentiation into effector and regulatory cells [11,12]. Along with the mTOR pathways, SCFA also enhance the activation of STAT3 (Signal transducer and activator of transcription 3), which is involved in the expression of cytokines (IL-10, IL-17, and IFN-γ) in T cells [12]. Collectively, these have the potential to alter the differential balance of Th1 versus Th2 immune differentiation, and as a consequence reduce the risk of allergic responses [11,12].

Two of the most studied prebiotics to date are galacto-oligosaccharides (GOS) and fructo-oligosaccharides (FOS). GOS are obtained either by synthesis or by extraction and hydrolysis of plant sources like pulses (α-GOS) or lactose (β-GOS) [13]. FOS are produced either by enzymatic synthesis or by hydrolysis of inulin from natural sources mainly from roots of chicory, artichoke, yacon, dahlia or agave [13]. Randomised controlled trials (RCTs) investigating the effects of GOS and FOS supplemented infant formula have found an increase in commensal *Bifidobacterium* growth [14,15,16,17], and reduced infant eczema incidence [18,19]. However, another RCT by Boyle et al. [20] found no reduction in infant eczema development, and a systematic review and meta-analysis which included 10 intervention trials (*n* = 4242 participants) using prebiotic supplemented infant formula found no overall reduction in eczema outcomes until four years of age (RR 0.75; 95% CI 0.56–1.01; I^2^ = 57%) [21]. Thus, the benefits of using infant prebiotic supplementation in the post-natal period as an allergy prevention strategy remain inconclusive. 

During pregnancy, there is close immunological interaction between the mother and her child providing enormous opportunities to influence fetal immune development [22,23,24]. Human fetal T cells are responsive to immune stimulation as early as 22 weeks’ gestation [25], and differences in immune function at birth in newborns who develop allergic disease indicates that ‘the scene is set’ to some extent by birth [26,27,28]. With evidence the fetal immune system is highly active and responsive to the mother and her diet, it is therefore logical to suggest that intervention with allergic disease prevention strategies during the in-utero period will have beneficial effects on later-life immune health. 

Animal models suggest that prebiotic fibre intake during pregnancy may influence immune programming in-utero and prevent allergic disease [10,29,30,31,32,33,34,35,36]. However, evidence in human studies on prebiotic fibre intake during pregnancy is still limited. Although two small human RCTs [37,38] have supplemented maternal diets with GOS and/or FOS from 25–26 weeks’ gestation, and found increased maternal faecal *Bifidobacterium* in the prebiotic compared to the placebo group, no child clinical allergic disease outcomes were assessed. One human observational study [10] has found an association between higher maternal dietary fibre intakes during pregnancy, increased maternal SCFA acetate levels, and reduced respiratory symptoms in the offspring (number of visits to the general practitioner for cough or wheeze). The observational findings from Thorburn et al. [10], along with the evidence from animal studies, support the need for well-designed RCTs to investigate the effect of maternal prebiotic intakes during pregnancy on child clinical allergic disease outcomes. Hence, the aim of this trial is to assess the effect of maternal prebiotic fibre dietary supplementation from 18–20 weeks’ gestation to six months’ post-partum to reduce the risk of child allergic disease development. The evidence generated from this trial will establish whether modulating the maternal diet and gut microbiota is a viable new earlier approach in the greatly needed strategies to prevent allergic diseases.

## 2. Trial Population and Methods

### 2.1. Trial Design and Ethical Approvals 

This is a two-arm (1:1 allocation), parallel-design, double-blinded, superiority randomised controlled trial. The trial is registered with the Australian New Zealand Clinical Trial Registry (ANZCTR): ACTRN12615001075572. The trial is known as the SYMBA Study. Ethical approval was obtained through the Joondalup Health Campus Human Research Ethics Committee (HREC Approval number 1451r); the University of Western Australia also granted reciprocal ethical approval for the trial (RA/4/1/8137). This trial is nested within the ORIGINS Project birth cohort [39] based at the Joondalup Health Campus, Western Australia, and the sponsoring institution is the Telethon Kids Institute, Nedlands, Western Australia.

### 2.2. Participant Eligibility

The inclusion criteria for this study are: (1) pregnant women < 21 weeks of gestation, whose infants have a first-degree relative (mother, father or sibling) with a history of medically diagnosed allergic disease (asthma, allergic rhinitis, eczema and/or food allergy); and (2) ability to provide informed consent. The gestational age is calculated from first trimester ultrasounds, or, if not available, the date of the last menstrual period. The exclusion criteria for this study are: (1) maternal smoking during pregnancy [40]; (2) maternal age < 18 years; (3) women already consuming prebiotic supplements (>twice per week); and (4) women who have a diagnosed cow’s milk allergy or lactose intolerance.

### 2.3. Recruitment

Women participating in the ORIGINS Project birth cohort [39] at the Joondalup Health Campus are given the trial participant information pamphlet. Pregnant women birthing at other hospitals in Western Australia are also informed about the trial by display of approved advertising material, including hard copy flyers and posters, as well as via digital media, which direct potential interested participants to contact our research staff. The women are then telephoned to follow-up if they are interested in participating, screened for eligibility, given full explanation in lay terms and any of their questions answered about the study. The participant is required to provide written informed consent and are given a copy of the signed Consent Form. Consent is voluntary and free from coercion, and women may withdraw their involvement in the trial at any time without prejudice and wherever possible the reason for withdrawal is recorded. Once eligibility is confirmed, basic demographic information (maternal age, postcode) is collected to comply with CONSORT guidelines [41].

### 2.4. Randomisation and Allocation to Treatment Groups

Once written consent has been obtained, each participant is randomised to one of two groups and assigned a unique uninformative five-digit study identification number (Study ID) according to a randomisation schedule via a secure web-based randomisation process. The Study ID number also corresponds to a matching Study ID labelled box of study powder tins to be provided to that participant. The computer-generated randomisation schedule is stratified, using randomly permuted, size-balanced blocks, by maternal allergy status (history of medically diagnosed asthma, allergic rhinitis, eczema and/or food allergy) and maternal pre-pregnancy body mass index (BMI < 25 or ≥25). The randomisation schedule is prepared by an independent statistician not involved with trial participants or data analysis. Randomisation codes are maintained by researchers working independently of the trial. Investigators and participants will not be unblinded until all the participating infants have completed their 12 month of age outcome assessments.

### 2.5. Interventions

The participating women are randomised to either a prebiotics intervention group or maltodextrin placebo control group:The prebiotics (intervention) group: women are asked to consume 14.2 g per day of prebiotic powder (Galacto-oligosaccharides (GOS) and Fructo-oligosaccharides (FOS) ratio 9:1) from <21 weeks gestation until 6 months’ postnatal infant age;The maltodextrin (control) group: women are asked to consume 8.7 g per day of maltodextrin powder from <21 weeks gestation until 6 months’ postnatal infant age.

The daily dose amounts of each study powder were designed to ensure matching energy content of 143 KJ per day. Both study powders are mixed with food or beverage and consumed orally by the participating women once per day. During the randomisation appointment, the research staff demonstrate how to use and level of the provided study powder scoop in the tin accurately to measure out the daily study powder amount, using an example scoop and cow’s milk powder (not the actual allocated powder scoop). An information leaflet with study powder mixing instructions is provided to each participant at the appointment. The participants are instructed not to consume any other prebiotic products during the trial intervention period

### 2.6. Intervention Duration

The intervention period for this trial is from study entry (18–20 weeks gestation) until 6 months of lactation. We chose a pragmatic and realistic approach to the dietary intervention. This was carefully considered to replicate the likely ‘real life’ scenario where a maternal healthy ‘high prebiotic fibre diet’ would not cease at birth of the baby, but continue during lactation. Furthermore, a combined pre- and postnatal strategy may also have enhanced allergy preventive effects (as discussed in [22]).

### 2.7. Blinding

Participants, outcome assessors, research staff and data analysts are blinded to the randomisation group allocation. To maintain the blind, both the intervention (prebiotic) and control placebo (maltodextrin) powders are packaged in identical tins. Both study powders are similar in taste, texture and colour. The difference in daily dose weights are accommodated by the study powders having different size scoops. The scoops are concealed within the tins to ensure blinding. All study powders are manufactured, packaged, and labelled by the independent company, Danone, Netherlands, according to Good Manufacturing Procedures. The trial is an investigator-initiated project and Danone had no other involvement other than the provision of the study products. The study powder supplier packaged and coded both trial study powders with the unique five-digit Study ID number. This study powder supplier is not involved in the assessment process. Study powders are securely stored at Joondalup Health Campus and clearly labelled for research purposes.

### 2.8. Monitoring Adherence to Study Powder Ingestion

During the intervention period the research team maintain regular (in-person or telephone) monthly contact with participants to monitor and encourage study powder consumption adherence, as well as to answer any questions as they arise. If the participant stops taking the study powder, she is asked to provide a reason for ceasing study powder ingestion. The participating women return their unused powder tins for weighing at the end of the intervention period when their infant is six months of age.

### 2.9. Trial Outcomes

The primary outcome for this trial is infant medically diagnosed eczema by 1 year of age. 

The secondary clinical outcomes (all participants) are: Infant medically diagnosed IgE-mediated food allergies by 1 year of age.Infant medically diagnosed recurrent wheeze by 1 year of age.Infant allergic sensitisation to food and environmental allergens at 1 year of age.Maternal and infant skin barrier permeability at 36 weeks (maternal only), 3–4 and 6 months post-natal, and at 1 year of age (infant only).Maternal weight gain during the pregnancy and lactation intervention period, gestational length, and pregnancy complications (including gestational diabetes mellitus, pre-eclampsia and gestational hypertension).Infant birth anthropometrics and body composition.Infant weight gain and growth during infancy.The secondary laboratory outcomes are:Maternal immune responses at 20, 28 and 36 weeks of gestation.Maternal gut microflora colonisation patterns and stool short-chain fatty acid levels and composition during the pregnancy and lactation intervention period.Infant gut microflora colonisation patterns and stool short-chain fatty acid profiles at 2, 3–4, 6 and 12 months of age.Infant immune responses at birth, 3–4, 6 and 12 months of age.Breast milk composition and immune components at 2, 3–4, 6 and 12 months of age.

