### 2.12. Study Timeline

Figure 1 summarises the participants schedule of appointments and biological sample collections. Before 21 weeks’ gestation, informed consent including a screening form checklist is completed. At 18–20 weeks’ gestation baseline data are recorded, including basic demographic information; maternal, paternal and any sibling history of allergic disease; maternal and paternal ethnicity and education; and any prior prebiotics or probiotics supplements use. Maternal weight and height are measured, and pre-pregnancy weight recorded. Baseline blood and stool samples are collected. 

Each month during the intervention period, from 18–20 weeks’ gestation until 6 months’ post-partum, the participating women are asked about their compliance with the study powder ingestion, any adverse gastrointestinal symptoms, stool frequency and consistency, any use of other prebiotics, probiotics or antibiotics, and any hospitalisations for >24 h duration. Maternal in-person appointments in pregnancy also occur at 28 and 36 weeks’ gestation, when weight and TEWL (36 weeks only) are measured, and blood and stool samples are collected.

After birth, data on infant sex, birth weight, length, head circumference, and mode of delivery details are collected. Infants also have a body composition measurement up to 96 h after birth. A sample of cord blood is collected where possible at delivery. 

Postnatal telephone calls occur at 1, 2 and 5 months of age. Data are also collected to prospectively capture information on infant feeding and to document any infant allergy symptoms. At the 1 month phone call, participants are reminded to collect a breast milk sample, as well as a maternal and infant stool sample when the infant is 2 months of age. These are frozen in the home freezer until they are brought in at the 3–4 month visit.

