### 2.16. Statistical Analysis

Analyses will be performed on an intention-to-treat basis (i.e., all randomised women analysed as randomised). For the primary outcome, the proportion of infants with medically diagnosed eczema by 12 months of age will be compared between groups using log binomial regression. Adjustment will be made for variables used to stratify the randomisation, with the difference between groups expressed as an adjusted relative risk with a confidence interval and two-sided *p*-value. Differences in secondary clinical outcomes will be examined in the same way. A sensitivity per-protocol analysis of the primary outcome will be undertaken in women that consumed at least 75% of their allocated study powder (based on return weights) during the entire intervention period (<21 weeks gestation to 6 months post-natal). Another sensitivity per-protocol analysis of the primary outcome will be undertaken in women that consumed their allocated study powder on at least 75% of the days between randomisation and 36 weeks of gestation (last clinic visit prior to birth).

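### Maternal weight gain and birth size are adjusted for maternal size only as BMI below or above 25, although height and both weights are collected at baseline; a modest precision gain is left unused

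*Protocol article*

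**What the plan says.** Four places in the protocol article bear on this point.

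- **2.9 (outcomes).** The secondary clinical outcomes include "Maternal weight gain during the pregnancy and lactation intervention period, gestational length, and pregnancy complications" and "Infant birth anthropometrics and body composition".
- **2.16 (analysis).** The primary outcome "will be compared between groups using log binomial regression". The covariates are then named: "Adjustment will be made for variables used to stratify the randomisation". All secondary clinical outcomes are covered by one sentence: "Differences in secondary clinical outcomes will be examined in the same way".
- **2.4 (strata).** The stratifiers are maternal allergy status and "maternal pre-pregnancy body mass index (BMI < 25 or ≥25".
- **2.12 (baseline data).** At 18–20 weeks, "Maternal weight and height are measured, and pre-pregnancy weight recorded". Maternal weight is measured again at 28 and 36 weeks' gestation and at 3–4 and 6 months after birth.

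No section names continuous BMI, height or weight as a covariate.

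**The concern.** Maternal size is an obvious baseline predictor of how much weight a woman gains and how large her infant is at birth. The stated adjustment keeps only which side of 25 her BMI falls on. A single cut discards more than a third of the linear information in BMI and carries no direct information on height. These outcomes supply the trial's evidence on maternal and fetal growth effects of the powder, so a wider interval than necessary has some cost.

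The same sentence in 2.16 leaves a second matter open. Read literally, it assigns log binomial regression to outcomes measured in kilograms, centimetres or percentages. That model is for a binary outcome, so the method for these continuous outcomes is not properly fixed.

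**Working it through.** **The plan's own figure.** The only sample-size figure is for eczema (2.15): 30% against 20%, two-sided alpha 0.05, 80% power, with "two-arm (1:1 allocation" allocation. The pooled formula is

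n = [1.960·√(2·0.25·0.75) + 0.842·√(0.30·0.70 + 0.20·0.80)]² / 0.10² = 293.15 per group.

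The stated 293 reproduces (294 if rounded up; power at 293 is 79.98%). Then 293/0.9 = 325.6, so 326 per group and 652 in total. No power or precision is stated for the outcomes discussed here. Below, 2 × 293 = 586 is used only as a scale for expressing gains.

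**Information kept by the cut.** If a normal covariate is split with a proportion p on one side, the share of its r² that survives is f = φ(z_p)² / [p(1−p)]. At a 50/50 split f = 0.637; at 40/60 it is 0.622. The split at BMI 25 in this trial is not given.

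**Assumptions.** Every correlation below is assumed, since the documents give none. A linear model is also assumed, and height is taken as uncorrelated with BMI.

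**Maternal weight gain, continuous BMI added to the cut.** The variance ratio is (1 − r²)/(1 − f·r²), with f = 0.637.

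| assumed abs(r) with BMI | ratio | variance reduction | equivalent extra women on 586 |
|---|---|---|---|
| 0.2 | 0.9600/0.9745 = 0.985 | 1.5% | 9 |
| 0.3 | 0.9100/0.9427 = 0.965 | 3.5% | 21 |
| 0.4 | 0.8400/0.8981 = 0.935 | 6.5% | 41 |

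A simulation with skewed BMI (lognormal, assumed mean 26, SD 5.5, 53% at or above 25) gives 1.6%, 3.8% and 7.1%.

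**Maternal weight gain, starting weight added.** With equal SDs and correlation ρ between starting and later weight, a plain change score has variance 2σ²(1 − ρ). Adjusting for starting weight leaves σ²(1 − ρ²). The ratio is (1 + ρ)/2, or 0.975, 0.950 and 0.925 for ρ = 0.95, 0.90 and 0.85, a reduction of 2.5% to 7.5%. The BMI cut already takes part of this. In the simulation the remaining reduction is 1.2% to 3.7%. The BMI and starting-weight routes overlap and must not be added together.

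**Birth size, continuous BMI and height added to the cut.** The ratio is (1 − r_B² − r_H²)/(1 − f·r_B²).

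- r_B = 0.1, r_H = 0.2: 0.9500/0.9936 = 0.956, a reduction of 4.4%, worth about 27 infants on 586.
- r_B = 0.2, r_H = 0.3: 0.8700/0.9745 = 0.893, a reduction of 10.7%, worth about 70 infants.

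The skewed-BMI simulation gives 4.5% and 10.9%.

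**Where the birth-size gain comes from.** Replacing the cut by continuous BMI alone gives 0.4% (0.9900/0.9936) and 1.5% (0.9600/0.9745). Adding height alone to the cut gives 4.0% (0.9536/0.9936) and 9.2% (0.8845/0.9745). Height does most of the work.

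**In terms of power.** A comparison with 80% power would reach 82.0% if residual variance fell by 5%, and 84.0% if it fell by 10%.

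**The case against.** The strongest reply is that nothing here is wrong. Adjusting for the stratification variables is sound, a randomised comparison needs no further covariates to be valid, and a condensed article can leave outcome-specific covariates to an analysis plan that is not shown. Much of this stands. It makes the point an optional improvement, but it does not remove it, because 2.16 does name an adjustment set and extends it to these outcomes. The gain is also modest and rests on assumed correlations, and that stands too.

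A reader might infer more than the documents support:

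- **Pregnancy complications.** With prevalence 5–15% and a relative risk of 1.2–1.5 per SD of BMI (assumed), variance falls by only about 0.1–2%. Continuous covariates can also stop a log binomial model converging, so the change is not free there. No case is made for this outcome.
- **Gestational length.** No gain has been calculated for it, and it is not part of this point.
- **One weight gain taken across delivery.** The wording in 2.9 could be read that way, but it is a list entry and does not define a single difference. Section 2.12 schedules weights in both phases, so separate analyses are already possible.
- **Attained weight in place of gain.** With starting weight as a covariate in a linear model, attained weight and gain give the same treatment effect. The benefit comes from the covariate.
- **Baseline size wholly unused.** BMI does enter through the stratum. If gain is counted from study entry, the 18–20-week weight is already its starting value, with its coefficient fixed instead of estimated.

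**Conclusion.** The point holds as a minor one, for maternal weight gain and infant birth anthropometrics and body composition. As written, maternal size is carried only by the BMI category, while better baseline measurements are in hand. Under the assumed correlations, residual variance would fall by about 1–7% for maternal weight and about 4–11% for birth size. Most of the birth-size gain depends on the assumed height correlation of 0.2–0.3, so it says little about the BMI cut itself.

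The planned comparisons would not be biased. The eczema analysis and the 652 target are untouched. The literal assignment of log binomial regression to continuous outcomes may be no more than condensed wording, but the text does not settle it, and the same rewrite can deal with it.

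**What to change.** In 2.16, or in the analysis plan if it does not already say so:

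1. State a linear model, with a mean difference and confidence interval, for maternal weight gain and for birth anthropometrics and body composition.
2. Keep both stratification variables and add continuous pre-pregnancy BMI.
3. Add maternal height for the birth-size outcomes, and measured 18–20-week weight for maternal weight.
4. Report maternal weight change from 18–20 weeks separately to 36 weeks' gestation and to 6 months post-partum, each adjusted for the 18–20-week weight. Do not use the 36-week weight as a covariate, since it follows randomisation.
5. State how a missing baseline height or weight is handled.

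Leave pregnancy complications and gestational length out of this change.

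The cost is wording only: no new data, visits or participants. It should be dated before unblinding, which 2.4 places after the last 12-month assessment and 2.17 expects no earlier than about June 2023. If unblinding has already happened, the extra adjustment should be labelled supplementary.
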